### Enrollment

We defined the index hospitalization as the first presentation for ALI or CLI, since a hospital admission serves as an easily identified site for detection of such cases. Use of an index hospitalization is also advantageous (as compared to recruitment from vascular specialty clinics or wound centers) since it defines a population in whom health care resource utilization is high and in which quality outcomes staff now exist to facilitate initial and subsequent outcomes data collection. Patient enrollment is intended to be sequential and fully inclusive, with exclusions limited to non-provision of informed consent that are documented by a screening log.

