### Use of source documents and data abstraction

This is a prospective registry, and as such all sequential eligible patients with ALI or CLI who are hospitalized (defined as requiring an index leg revascularization procedure or overnight stay) will be entered into the registry. Medical record documentation will be required immediately on admission (not retrospectively) for establishment of the presence of ALI or CLI. Vascular specialty and hospitalist staff will receive instruction on: (a) the clinical definitions of ALI and CLI, (b) how to complete a source document on patient admission that includes the time of onset of symptoms, and (c) the use of health system tools (e.g., standardized order sets) to facilitate prompt measurement of pedal or great toe pressures (Table 1).

A documented medical history of coronary artery disease (CAD) will consist of 1 or more of any of the following chart documented conditions or procedures: stable angina, previous myocardial infarction, history of percutaneous coronary intervention or history of coronary artery bypass graft surgery. Documented cerebrovascular disease (CVD) will be defined by a history of transient ischemic attack (TIA), ischemic or hemorrhagic stroke, carotid stenting or carotid endarterectomy. Documented prior PAD will be defined by 1 or more of the following criteria: symptomatic PAD defined by history of claudication, asymptomatic PAD documented in the medical records, or history of ALI or CLI.

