### Key time segments

The symptom onset of an initial episode of ALI/CLI is defined by the patient’s self-report provided to the vascular specialist at hospital admission, is dictated into the encounter note, and this note (date and time) is later abstracted from the medical records. Vascular specialists (vascular surgeons, vascular medicine specialists, and interventional radiologists) are instructed to document the patient-reported index limb symptom onset within pre-specified time parameters: within one hour for patients presenting within 3 days, within one day for patients presenting within 3 to 30 days, and within one week for patients presenting greater than one month since symptom onset. For CLI patients who cannot state an exact time of leg symptom onset, it will be assumed that the onset time is 12 noon on the day specified. Inasmuch as ALI or CLI is known to recur (repeat episodes are common), the index leg symptom is arbitrarily defined as that which is temporally closest to the index hospitalization. This approach is similar to that used for ACS or stroke health services research.

While the pre-admission symptom duration serves as the primary pre-defined hypothesized predictor of advanced PAD health outcomes, a number of other clinical care time segments are considered of potential utility in evaluation of the efficiency of hospital-based PAD care, as it is known that CLI hospitalizations are lengthy (greater than seven days) and expensive [15]. The “admission to ABI/TBI” time segment is defined as the time from hospital arrival to initiation of the first hospital-based pedal or toe pressure measurement. The “admission to heparin” time is defined as the time from hospital arrival to the chart-documented initiation of a therapeutic intravenous heparin infusion for patients so treated. The “admission to vascular specialist at bedside” time segment is defined as the time from hospital arrival until the patient is evaluated by a vascular specialist, and this is set by the time of the dictated note. The “admission to revascularization” time segment is defined as the time from hospital arrival until the patient enters the operating room or catheterization laboratory, and includes only the use of an endovascular procedure, surgical procedure or primary amputation (medical treatment alone is not included in this definition). Hospital length of stay is defined as the number of days of hospitalization from admission to discharge.

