**Demographic, clinical and functional characteristics, and key time segments**						
Demographic variables						
	Race, gender, education	X				
	Marital and employment status	X	X	X	X	X
Physical examination (weight, height, blood pressure, heart rate and rhythm)		X				
Laboratory values (serum creatinine, hemoglobin, fasting lipid profile)		X				
Etiology of ALI-CLI		X				
Key time segments (see ‘List of key time segments’)		X	X			
Length of hospital stay			X			
Endovascular and open surgical procedures			X			
Ambulatory status		X	X	X	X	X

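### Admission to revascularization is timed from hospital arrival for booked and unplanned admissions alike, so a pooled association with outcome could reflect admission route instead of in-hospital delay

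*Protocol article*

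**What the plan says.** All references are to the protocol article.

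- **Clock.** Under Key time segments, admission to revascularization is "defined as the time from hospital arrival until the patient enters the operating room or catheterization laboratory". The same arrival clock starts the segments for ABI/TBI, heparin and vascular specialist. No definition differs by type of admission.
- **Who enters.** Under Use of source documents and data abstraction, eligible patients are those "hospitalized (defined as requiring an index leg revascularization procedure or overnight stay". Under Enrollment, "Patient enrollment is intended to be sequential and fully inclusive, with exclusions limited to non-provision of informed consent". A patient brought in for a booked leg procedure therefore qualifies, although the article never uses a word such as elective or scheduled.
- **Data collected.** Table 2 lists "Key time segments (see ‘List of key time segments" among its items, and no item for route of admission.
- **Use.** Under Statistical analysis, key time variables are analysed both as continuous measures and in categories to look for dose-response. They are exposures in logistic models for short-term amputation, MI, stroke and death, and time segments are exposures in linear models for length of stay. Candidate confounders come from three broad groups (demographics, clinical features, risk factors). Admission route is not named.
- **Rank.** Key time segments makes pre-admission symptom duration the primary predictor. The in-hospital segments are offered as possibly useful for judging how efficiently the hospital delivers care.

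**The concern.** One variable carries two meanings. A CLI patient worked up in clinic and admitted for a booked procedure reaches the operating room or catheterization laboratory a short time after arrival, however long the outpatient wait was. For a patient admitted unplanned, the same interval records what the hospital did after arrival.

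If planned and unplanned patients also differ in prognosis, admission route is associated with both exposure and outcome and confounds the pooled model. Length of stay is open to the same problem, because a booked procedure can shorten both the time to the procedure and the stay.

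The registry's declared purpose is to find health-system targets for later trials. A scheduling pattern could be reported as evidence for or against faster in-hospital revascularization.

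**Working it through.** The article states no sample size, event count or case mix, so there is no figure of its own to reproduce. The check has two parts.

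**1. Which segments make a booked patient look fast?**

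- *Revascularization:* the interval ends on entry to the procedure room, so a booked patient's time is short by design.
- *ABI/TBI:* the interval is "the time from hospital arrival to initiation of the first hospital-based pedal or toe pressure measurement". A pressure taken earlier in clinic does not count, so a booked patient may be late or have no value.
- *Vascular specialist:* the interval is "the time from hospital arrival until the patient is evaluated by a vascular specialist, and this is set by the time of the dictated note". An outpatient evaluation does not count, and the timing of the note can go either way.
- *Heparin:* the interval ends at "initiation of a therapeutic intravenous heparin infusion for patients so treated". It exists only for those patients.

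The short-by-appointment problem is therefore clear for admission to revascularization only. For ABI/TBI and specialist the problem is one of coding.

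**2. How large could the confounding be?**

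Every input is an assumption. The risks are chosen with an eye to the one-year mortality ranges quoted in the Discussion (16-42% for ALI, 20-25% for CLI), which are not given by admission route.

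- p = share of admissions planned: 0, 20, 40 or 60%
- f_P = planned patients in the procedure room within 24 h of arrival (fast): 95%
- f_U = unplanned patients who are fast: 20, 40 or 60%
- r_U and r_P = event risk in unplanned and planned patients: 25% and 20%, 35% and 20%, or 42% and 16%
- Time has no effect within either route.

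Formulas:

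- F = p·f_P + (1−p)·f_U
- Risk if fast = [p·f_P·r_P + (1−p)·f_U·r_U] / F
- Risk if slow = [p·(1−f_P)·r_P + (1−p)·(1−f_U)·r_U] / (1−F)
- OR = odds if slow / odds if fast

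Worked case: p = 0.40, f_U = 0.40, r_U = 0.35, r_P = 0.20.

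- F = 0.38 + 0.24 = 0.62
- Risk if fast = (0.38×0.20 + 0.24×0.35)/0.62 = 0.160/0.62 = 25.8%
- Risk if slow = (0.02×0.20 + 0.36×0.35)/0.38 = 0.130/0.38 = 34.2%
- OR = (0.342/0.658)/(0.258/0.742) = 1.50

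Crude OR, slow versus fast (each range runs over f_U from 60% down to 20%):

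| Planned | Risks 25% / 20% | 35% / 20% | 42% / 16% |
|---|---|---|---|
| 0% | 1.00 | 1.00 | 1.00 |
| 20% | 1.07-1.16 | 1.19-1.45 | 1.32-1.84 |
| 40% | 1.13-1.23 | 1.36-1.70 | 1.66-2.43 |
| 60% | 1.17-1.25 | 1.50-1.82 | 1.96-2.78 |

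Planned patients make up 28-54% of the fast group at 20% planned, and 51-76% at 40%.

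*Reversal.* Swap the risks in the worked case (planned 35%, unplanned 20%). Risk if fast = (0.38×0.35 + 0.24×0.20)/0.62 = 0.181/0.62 = 29.2%. Risk if slow = (0.02×0.35 + 0.36×0.20)/0.38 = 0.079/0.38 = 20.8%. OR = (0.208/0.792)/(0.292/0.708) = 0.64.

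*Within route.* Fast and slow patients share one risk by construction, so the OR is 1.00 in each stratum.

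**The case against.** The strongest reply is that this is a condensed article on a hypothesis-generating pilot registry. The standardized case report form and the data-element standard it cites are not shown, the clinical covariate group is broad enough to hold admission type, and the models are adjusted for confounders. The in-hospital segments are also secondary. This is fair, and it limits the weight of the point. It does not remove it: the arrival clock and the entry rule are stated, they apply to everyone, and adjustment helps only if route is recorded and used. A split by ALI and CLI would not settle it either, since planned and unplanned admissions can mix within CLI.

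The reply is also right that no input to the illustration comes from the article, that the odds ratios are crude and anchored on one-year risks while the logistic models concern short-term outcomes, and that no text says planned patients do better. The Discussion describes CLI prognosis as comparably poor to that of ALI.

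A reader might infer three stronger claims, which the article does not support:

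- *That every in-hospital segment marks booked patients as fast.* The definitions show otherwise for ABI/TBI, specialist and heparin.
- *That the segments do not measure delay.* For ALI and other unplanned admissions, arrival is a valid start.
- *That the primary predictor is spoiled because it includes time under outpatient care.* The stated exposure is the duration of limb ischemia symptoms before hospital, and a limb under outpatient care is still ischemic. Splitting the interval at first medical contact would be a further research question, not a correction.

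**Conclusion.** The concern holds for admission to revascularization. Pooled over all admissions, that segment mixes scheduling with in-hospital delay, and nothing in the article separates the two.

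With 20-40% planned admissions and lower risk in planned patients, the illustrative spurious odds ratio is about 1.1 to 2.4. It falls below 1 if planned patients are at higher risk, and is exactly 1 if none are planned. These figures show that the effect could matter; they do not estimate it, because the share planned, the risk by route and the share treated quickly are all assumed.

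For the ABI/TBI and specialist segments, the narrower conclusion is that earlier outpatient tests and evaluations need their own code. The primary hypothesis is untouched. This is a worthwhile correction to a secondary analysis and does not threaten the registry's main aim.

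**What to change.** 1. Abstract admission type from the chart: planned, unplanned direct, or transfer. If the case report form already holds this item, say so and name it in the analysis.
2. Analyse admission to revascularization within admission type, by stratification or adjustment, for the clinical outcomes and for length of stay. Take unplanned admissions as the main reading of in-hospital delay. Dropping planned admissions altogether is unnecessary and loses patients.
3. For ABI/TBI and vascular specialist, give patients already tested or evaluated as outpatients before admission a separate code, so that they are not scored as late or missing.
4. Leave symptom onset to admission as defined.

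The cost is one extra abstracted field, back-abstraction for patients enrolled since recruitment began in February 2007, the separate coding in step 3, and less precision within strata. No sample size or power figure changes, since the article gives none.

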#### List of pre-specified “key time segments” for patients with advanced peripheral artery disease

Symptom onset to admission

Admission to ABI/TBI measurement

Admission to IV heparin administration

Admission to vascular specialist at bedside

Admission to revascularization

Length of stay (days)

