### Study outcomes

The study outcomes that will be evaluated are summarized in Table 2. The systemic ischemic risk clinical outcomes include: nonfatal MI, nonfatal stroke, cardiovascular (CV) death, all-cause death, and cardiovascular re-hospitalization event rates. The limb ischemic risk clinical outcomes include: ALI or CLI recurrence, minor or major amputation, and total amputation event rates. These individual outcomes will be used to derive a composite triple endpoint (defined as any nonfatal MI, stroke or amputation) and quadruple endpoint (defined as any non-fatal MI, stroke, amputation or death). As well, the relevant clinical outcome of “amputation-free survival” time will be calculated at one year.

**Table 2 T2:** Clinical evaluations on admission and at 1-, 6- and 12-month follow-up

		**Admission**	**Hospital discharge**	**1 month**	**6 month**	**12 month**

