**Outcome events**						
Amputation (major or minor)			X	X	X	X
Cardiovascular ischemic events (non-fatal MI and stroke), death			X	X	X	X
Recurrence of ALI-CLI			X	X	X	X
Other causes of hospitalization				X	X	X

“Minor amputation” is defined as removal of any part of the lower limb below the ankle and “major amputation” is defined as removal of part of the lower limb above the ankle. All-cause death is ascertained via the social security death index (SSDI) in the USA or via other national death registry systems using a combination of the social security number (SSN), name and birth date to identify cases. Searching the online SSDI, with a correct SSN provides an accurate method to determine death as an outcome in clinical research studies. A majority of subjects ordinarily lost to followup including those with sudden death outside the hospital can thus have their vital status accurately determined [16]. Cardiovascular death includes fatal stroke, fatal MI, and other cardiovascular death. Other cardiovascular death includes deaths of cardiac origin: death associated with pulmonary embolism, vascular operation or procedure, amputation (except for trauma or malignancy), heart failure and visceral or limb infarction. Re-hospitalization for CV events is defined as hospitalization for transient ischemic attack, unstable angina, worsening of PAD, CHF, other ischemic arterial event or bleeding leading to both hospitalization and transfusion. Recurrence of ALI/CLI is defined as occurrence of any second episode of clinically diagnosed ALI/CLI and ascertained by medical chart review at follow-up.

Follow-up will be performed primarily by phone calls at 1 month (with a one week window), 6 months (with a one month window), and 12 months (with a two month window) after hospital discharge using a phone script containing standardized questions. The occurrence of non-fatal MI, non-fatal stroke, amputation, re-hospitalization, recurrence of ALI/CLI are ascertained by medical records, all cause death by social security death index website [17], and CV death by medical record review. Ambulatory status will be ascertained by self-report during follow-up calls and at return visits.

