### Statistical analysis

Descriptive statistics will be presented as means and standard deviations for continuous variables, and frequencies and percentages for categorical data. Continuous data that are not normally distributed will be analyzed by nonparametric methods. Key time variables will be analyzed as continuous variables, and also categorized to allow assessment of dose–response patterns. Univariate models for all outcome variables with demographic, clinical and risk factor variables will be used to elucidate potential confounding variables. Multivariable logistic regression models will be used to assess the association between key time variables and short-term binary outcomes (amputation, MI, stroke and death), with adjustment for confounders. Survival analysis will be performed using Kaplan-Meier methods for preliminary analyses, and Cox proportional hazards models with adjustment for confounders. Multiple linear regression models will be used to assess the associations between time segment variables and length of stay, with adjustment for confounders. A two-sided p-value of <0.05 will be considered statistically significant. Data analysis will be performed using Stata (Stata Inc, College Station, TX, USA).

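### Primary amputation ends the admission-to-revascularization segment and is also an outcome regressed on it, so this secondary segment's association with amputation may be distorted in either direction

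*Protocol article*

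**What the plan says.** Five places in the protocol article bear on this.

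- **Key time segments.** The segment runs from hospital arrival to entry into the operating room or catheterization laboratory. It "includes only the use of an endovascular procedure, surgical procedure or primary amputation (medical treatment alone is not included in this definition"). Admitting primary amputation is therefore explicit. The same section makes pre-admission symptom duration the primary hypothesized predictor and presents the other segments mainly as measures of the efficiency of hospital care.
- **List of pre-specified key time segments.** "Admission to revascularization" is one of the six entries.
- **Study outcomes.** The limb outcomes include "minor or major amputation, and total amputation event rates". Amputation also enters the triple endpoint ("defined as any nonfatal MI, stroke or amputation") and the quadruple endpoint, which adds death. Amputation-free survival time is calculated at one year.
- **Table 2, Outcome events, and the definitions after it.** "Amputation (major or minor") is recorded from hospital discharge onward, so an index-stay amputation counts. Amputations are classified by anatomical level only: a major amputation "is defined as removal of part of the lower limb above the ankle". Primary and later amputation are not distinguished.
- **Statistical analysis.** Multivariable logistic models will "assess the association between key time variables and short-term binary outcomes (amputation, MI, stroke and death"), with the times used both as continuous variables and in categories.

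**The concern.** Primary amputation does not restore flow, so the name of the segment and its definition disagree. That would be only a labelling matter if the segment were used descriptively. It becomes an analytical problem because the same event then serves as an outcome in a model with this segment as exposure. A patient whose clock stops at primary amputation has the amputation outcome at that instant, with probability 1. The coefficient for time then mixes two things: any relation between delay and limb loss among revascularized patients, and the difference in waits between patients sent to primary amputation and the rest. Adjustment for baseline confounders does not separate them, because the problem lies in the definition of the variable.

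The registry is meant to identify health-system targets and to supply estimates for future trials, and the Discussion lists key time segments among the contributors to amputation to be evaluated. An artefactual in-hospital delay effect, harmful or protective, could be carried into that work.

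**Working it through.** **1. What the text settles.** For a patient whose first procedure is primary amputation:

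| Role | Source in the article | Event |
|---|---|---|
| End of the exposure time | Key time segments | primary amputation |
| Outcome | Study outcomes; Table 2 from discharge | the same amputation |
| Model joining them | Statistical analysis, logistic regression | amputation on key time variables |

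No passage removes these patients from the exposure or the outcome, or starts amputation follow-up after the index procedure. For amputation the link is named in the model sentence. For the composites and amputation-free survival it arises wherever the segment is carried into those analyses.

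**2. How large it could be.** The article states no sample size, event rate or waiting time, so there is no figure to reproduce. Everything below is assumed, for illustration:

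- f = share with primary amputation as first procedure: 10%
- q = later amputation risk among revascularized patients: 12% or 15%, unrelated to time (true null)
- log-normal time with log-scale SD 0.9 to 1.2
- r = typical time to primary amputation divided by typical time to revascularization
- n = 300, unadjusted logistic regression of amputation on log2(time)

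*Share of amputations that are the same event as the end of the exposure:* s = f / [f + (1 − f)q].

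- q = 12%: 0.10 / (0.10 + 0.90 × 0.12) = 0.10 / 0.208 = 48%
- q = 15%: 0.10 / (0.10 + 0.90 × 0.15) = 0.10 / 0.235 = 43%

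*Approximate spurious slope per doubling:* the difference in mean log2(time) between cases and non-cases, divided by the variance, so b ≈ s · log2(r) / (SD / ln 2)².

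- q = 12%, SD 0.9, r = 2: 0.481 / 1.686 = 0.285, so OR ≈ 1.33 (simulated 1.32)
- q = 15%, SD 1.2, r = 2: 0.426 / 2.997 = 0.142, so OR ≈ 1.15 (simulated 1.15)

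*Simulated odds ratio per doubling (approximate z at n = 300):*

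| q | SD | r = 0.5 | r = 1 | r = 2 |
|---|---|---|---|---|
| 12% | 0.9 | 0.76 (−2.5) | 1.00 | 1.32 (2.5) |
| 12% | 1.2 | 0.85 (−1.9) | 1.00 | 1.17 (1.9) |
| 15% | 1.0 | 0.82 (−2.1) | 1.00 | 1.22 (2.1) |
| 15% | 1.2 | 0.87 (−1.8) | 1.00 | 1.15 (1.8) |

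In the 15%, SD 1.0 case, the rejection rate against the nominal 5% was 54% for r = 2, 56% for r = 0.5 and about 5% for r = 1. With f = 5% and r = 2 the odds ratio was 1.13 (rejection 24%); with f = 20% it was 1.34 (92%). A modest difference in waits, r = 1.25 with q = 12% and SD 0.9, gives about 1.10 (z about 0.8).

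**3. What simple exclusion does.** Dropping primary-amputation patients returns an odds ratio of about 1.00 here, but the simulation builds that in, since later risk was made independent of time. In a second scenario, delay acted only by raising the odds of primary amputation, by 1.5 per doubling (about 9% primary amputation, q = 12%, SD 0.9). The all-patient odds ratio for amputation was 1.20, and after exclusion it was 1.00. Exclusion alone can therefore erase a real effect.

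**The case against.** The strongest reply is that the segment is secondary and openly defined. The article puts pre-admission symptom duration first and offers the other times largely as efficiency measures. For that purpose, and for the length-of-stay regression, time to the first definitive procedure including amputation is reasonable. The registry is a pilot that generates hypotheses and makes no power claim. All of this stands, and it limits the importance of the point. It does not remove it, because the Statistical analysis section also uses the key times to model amputation.

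A second reply is that the exposure is a duration, not the fact of amputation, so overlap alone creates no association. This also stands: with equal waits the odds ratio is 1.00. A third is that the figures depend on shares, waits, spread and sample size that the article does not give, and on an unadjusted model. That is correct, and they serve only as illustration.

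A reader might go further and infer that the delay analysis is circular throughout, that the registry's main hypothesis is compromised, or that primary amputation is being coded as a revascularization strategy. The article supports none of these. The overlap is confined to patients whose first procedure is primary amputation and to outcomes that contain amputation. The primary predictor does not use this clock. The inclusion occurs only in the definition of a time segment, and Table 2 lists endovascular and open surgical procedures in their own row.

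**Conclusion.** The point holds as a local defect of definition. One event can both close the admission-to-revascularization segment and count as the outcome modelled on it. The associations exposed are those of this secondary segment with amputation, the triple and quadruple composites and amputation-free survival. MI, stroke and death as single outcomes, length of stay, and everything based on symptom onset to admission are not made circular.

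The direction is unknown and the size depends on how far waits differ. It is nil if they are equal. For a twofold difference, under the assumptions listed, it is an odds ratio per doubling of about 1.15 to 1.3 or 0.76 to 0.87. At 300 patients that is borderline or nominally significant under no true effect (|z| about 1.8 to 2.5). It is worth correcting because the change is small, but it does not undermine the registry's main question.

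**What to change.** **Key time segments.** Limit admission to revascularization to endovascular or open surgical revascularization. Record admission to primary amputation as a separate segment, and add it to the list. A combined time from admission to first definitive procedure may be kept, under that name, for efficiency and length-of-stay analyses.

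**Statistical analysis.** For outcomes that contain amputation, relate the revascularization segment to amputation occurring after the index procedure. Report alongside it an analysis of all admitted patients from admission, with revascularization as a time-dependent state and primary amputation as an event (or competing event) at its date.

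**Cost.** A sentence or two in each section, a recode and one added model. Table 2 already has procedures and amputations recorded at discharge; procedure dates are needed, and the existing segment already requires them. The segment analysis loses some patients and conditions on having been revascularized, so by itself it cannot show delay that leads to primary amputation. The all-patient analysis covers that, and the two should be reported together. Patient care is unaffected.
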